**Secondary:**

- Time to a normal body temperature [ Time Frame: From the time of randomization until the time of normal body temperature, assessed up to 15 days]
- Time to the alleviation of nasal/throat/chest symptoms [ Time Frame: From the time of randomization until the time of absence of nasal/throat/chest symptoms, assessed up to 15 days
- Proportion of participants in each group with normalization of fever [ Time Frame: day 7 and day 15 ]
- Proportion of participants in each group with oxygen saturation > 94% on room air for >24h [ Time Frame: day 7 and day 15 ]
- Time to fever normalization (if febrile at baseline) [ Time Frame: within 15 days ]
- Time to first negative SARS-CoV-2 PCR in NP swap (if pos. at baseline) [ Time Frame: within 15 days ]
- Time to first negative SARS-CoV-2 PCR in lower respiratory tract specimens (sputum, bronchoalveolar lavage, tracheal aspirate) (if positive at baseline) [ Time Frame: within 15 days ]
- Duration of oxygen therapy [ Time Frame: within 30 days ]
- Proportion of participants in each group with need for mechanical ventilation [ Time Frame: within 30 days ]
- Duration of hospitalization [ Time Frame: within 28 days ]
- All cause mortality [ Time Frame: day 30 ]

**Study Center(s):** Study in Indian population and recruitment will happen up to 5 research sites based on competitive patient recruitment.

**Phase of Development:** Proof of Concept/ Intervention Trial on traditional medical product.

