**Study Period:**

Estimated time of first subject enrollment: 1 Q 2020

Estimated time of last subject enrollment: 1Q 2020

Number of Subjects (planned): Approximately 112 randomized subjects with assumed drop-outs of 10%; 100 evaluable subjects.

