**Secondary Efficacy Endpoint:**

- Proportion of Participants experiencing Treatment-Emergent Adverse Events [Time Frame: First dose date up to 15 days]
- Changes in Haematological and Biochemical parameter like CBC,ESR, CRP, Troponin, Liver function test, Renal function test, [Time Frame: First dose date up to 15 days]
- Changes in inflammatory markers - IL2, IL6, Interferon α, IgG, IgM
- Significant changes in the Chest X-Ray before and after treatment.

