**Statistical Methods:**

The total sample size is 112 randomized subjects. This sample size is allocated to treatment arms in a 1 to 1 ratio. This sample size provides 50% power if the following assumptions are made based on earlier reviews. SAS 9.4 statistical analysis software will be used for statistical analyses. T-test will be used for comparisons between groups for continuous variables. The comparison between groups for categorical variables will be performed using Fisher's exact probability method. Means and standard deviations will be used to describe centralized discrete trends. The t-test, rank-sum test, and Fisher's exact probability method will be used for comparisons between groups. P 0.05 indicates that the difference was statistically significant.

**RANDOMIZED CONTROLLED SINGLE BLINDED PROSPECTIVE MULTI CENTRE CLINICAL TRIAL TO INVESTIGATE THE SAFETY AND EFFICACY OF ZINGIVIR-H AS AN ADJUVANT THERAPY IN HOSPITALIZED ADULTS DIAGNOSED WITH CORONAVIRUS DISEASE 2019 (COVID-19).**

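### Fisher's exact test for the binary secondary and safety outcomes is valid but conservative at about 50 per arm; a suitably defined Boschloo test recovers some power at no cost in type I error

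*Protocol*

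**What the plan says.** The Statistical Methods section of the Synopsis assigns one test to categorical outcomes: "The comparison between groups for categorical variables will be performed using Fisher's exact probability method". A later sentence lists the full set: "The t-test, rank-sum test, and Fisher's exact probability method will be used for comparisons between groups". It does not say which endpoint takes the rank-sum test. The threshold is given as "P 0.05 indicates that the difference was statistically significant", with no sidedness.

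Several outcomes covered by the categorical rule are binary. The secondary objectives include "Proportion of participants in each group with need for mechanical ventilation", and also fever normalization, oxygen saturation above 94% and mortality. The secondary efficacy endpoints include "Proportion of Participants experiencing Treatment-Emergent Adverse Events".

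On size, the Study Period section gives "Approximately 112 randomized subjects with assumed drop-outs of 10%; 100 evaluable subjects", and Statistical Methods adds "This sample size is allocated to treatment arms in a 1 to 1 ratio". On power it says "This sample size provides 50% power if the following assumptions are made based on earlier reviews", but no effect size or event rate follows.

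**The concern.** Fisher's test conditions on the total number of events. With few events only a few tables are possible, so the attainable significance levels are coarse and the test usually runs well below its nominal 5%. The shortfall is largest for uncommon outcomes, which here are likely to include ventilation, death and serious adverse events.

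What is at stake is power in a small trial. An unconditional exact test can use the unspent part of the 5% without exceeding it. Because the protocol names Fisher's test outright, this is a stated choice and not a detail left to a later analysis plan.

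**Working it through.** **Inputs.** From the Protocol: 100 evaluable subjects, 10% drop-out, 1:1 allocation, threshold 0.05. Assumed: a two-sided test, and all event rates, since the Protocol gives none.

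**The plan's own figure.** 100 / (1 − 0.10) = 111.1, rounded up to 112. This matches. It gives 112 / 2 = 56 randomized and 100 / 2 = 50 evaluable per arm. The stated 50% power cannot be reproduced without an effect size.

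**Fisher p-value.** For x events among n1 and y among n2, with t = x + y, let h(k) = C(n1,k)·C(n2,t−k) / C(n1+n2,t). The two-sided p-value is the sum of all h(k) no larger than h(x).

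Two cases can be checked by hand:

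- 0/50 v 5/50: h(0) = C(50,5)/C(100,5) = 2,118,760 / 75,287,520 = 0.0281. The opposite extreme is equally likely, so p = 2 × 0.0281 = 0.056, which is not significant.
- 4/48 v 0/52: h(4) = C(48,4)/C(100,4) = 194,580 / 3,921,225 = 0.0496. The opposite extreme is C(52,4)/C(100,4) = 270,725 / 3,921,225 = 0.0690. That is larger, so it is not added, and p = 0.0496, which is significant.

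The second case shows why slightly unequal arms make Fisher's test less conservative: the two extremes no longer tie.

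**True size.** For a common rate π, size(π) is the sum of Bin(x; n1, π)·Bin(y; n2, π) over all tables with Fisher p ≤ 0.05. Full enumeration gives:

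| Arms | π = 5% | π = 10% | Maximum over π |
|---|---|---|---|
| 50 v 50 | 0.72% | 1.79% | 3.52% |
| 56 v 56 | 0.92% | 2.02% | 3.27% |
| 48 v 52 | 2.2% | 3.1% | 4.4% |

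Below a 5% rate it falls further. At 50 per arm it is 0.17% for π = 3% and 0.04% for π = 2%.

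**Boschloo's test.** Take the two-sided Fisher p-value as the statistic, and find the largest cutoff c for which the maximum size over π is at most 5%. At 50 per arm c = 0.0693, with maximum size 4.87%. At 56 per arm c = 0.0736, with maximum size 4.82%. Because c is above 0.05, every table that Fisher's test rejects is rejected here too. The 0/50 v 5/50 table has Boschloo p = 0.035.

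**Power, Fisher to Boschloo, at assumed rates.**

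| Rates | 50 v 50 | Gain (points) |
|---|---|---|
| 1% v 5% | 2% to 7% | 4 |
| 2% v 8% | 9% to 18% | 8 |
| 2% v 12% | 31% to 44% | 13 |
| 2% v 14% | 44% to 57% | 13 |
| 5% v 15% | 24% to 32% | 8 |
| 5% v 20% | 51% to 58% | 7 |
| 10% v 30% | 64% to 70% | 6 |
| 20% v 40% | 52% to 56% | 5 |
| 30% v 50% | 46% to 53% | 7 |

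Gains are rounded from the unrounded powers. At 56 per arm, 5% v 20% moves from 58% to 68%. At 48 v 52, the pairs 2% v 14%, 5% v 20% and 30% v 50%, each taken in both directions, gain about 1 to 12 points.

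**Which two-sided rule.** Some software defines two-sided Boschloo by doubling the smaller one-sided p-value. For 4/48 v 0/52 that version gives p = 0.068, where Fisher's test gives 0.0496. So the guarantee of never doing worse than Fisher's test depends on the definition used above.

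**The case against.** The strongest case for leaving the text alone is that nothing in it is wrong. Fisher's test never exceeds 5%, is conventional for sparse tables, and contradicts nothing else in the Protocol. That stands: this is a preference on efficiency grounds.

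Three further objections also hold in part.

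- The event rates are assumed. A pair such as 2% v 14% is a sevenfold difference, and the 0/50 v 5/50 example sits close to the threshold. At more ordinary rates the gain is 5 to 7 points with equal arms, and it can be as small as 1 point at 48 v 52.
- The 0.7% to 3.5% range applies to exactly 50 per arm and common rates from 5% to 95%. The Protocol plans approximately 112 subjects with drop-out, so exact balance cannot be assumed.
- An unspecified switch to Boschloo could lose rejections that Fisher's test makes, as the 4/48 v 0/52 table shows.

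A reader might also infer that harms will be missed because of this test. The Protocol does not support that. Its Primary Safety Endpoints are listed without a hypothesis or decision rule, serious events are reported individually within 24 hours, and no harm conclusion depends on p < 0.05. For rare harms neither test helps much: 0/50 v 4/50 is non-significant under both (0.117 and 0.089).

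**Conclusion.** The point holds as a modest, nearly free improvement to a stated method. For binary outcomes at 50 per arm and two-sided 0.05, Fisher's test uses at most 3.5% of the 5% allowed, and about 0.7% when events occur in 5% of both arms. The unused part is worth about 4 to 13 points of power over the assumed rates. With arms of 48 and 52 the loss is smaller, but it does not vanish.

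Two wider readings should be resisted. The quoted sentence might be taken to cover every categorical outcome, including the 7-point ordinal primary endpoint. However, the dominance over Fisher's test is shown here only for 2x2 tables, and the rank-sum test also listed may be meant for that endpoint. Nor should the 50% power statement be tied to these outcomes: it names no endpoint or effect size, so it cannot show that they are powered at 50%.

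**What to change.** In Statistical Methods, limit the Fisher sentence to tables larger than 2x2 where it is wanted, and add wording along these lines: *Binary outcomes will be compared between arms by Boschloo's unconditional exact test at two-sided 0.05, using the two-sided Fisher exact p-value as the test statistic (not a doubled one-sided p-value) and computed for the actual arm sizes; the risk difference will be reported with its 95% confidence interval.*

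The interval matters at least as much as the test for the safety outcomes, since it shows which differences the data cannot exclude.

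The cost is one or two sentences and a little custom code in SAS 9.4: enumerate the tables for the realized arm sizes and maximize the size over the common rate. No data collection, sample size or type I error guarantee changes. The wording should be settled before outcome data are compared by arm.

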**BACKGROUND:**

The epidemic of SARS-CoV-2, causing the disease COVID-19 has expanded from Wuhan throughout China and is being exported to a growing number of countries including India, some of which have seen onward transmission. As per WHO total number of confirmed cases are 1,714,782 and 103,803 number of deaths were reported, and in India 5,734 corona virus cases and 166 deaths has been reported till April 11, 2020. In India COVID-19 causes serious threat with over 6634 confirmed cases with 242 deaths in the same timeline. The disease has shown to put an enormous burden on the society and is a challenge to the physician owing to its infectivity, complications, morbidity and absence of proper medication. As medicine is an ever-changing science new research and clinical experience broaden our knowledge and bring changes in drug therapy. COVID-19 is now spreading throughout the world because of its high infectivity and communicability. Also there is a lack in the proper management of the disease. So any contribution in the knowledge or treatment of COVID-19 from any source could be of great value to the medical profession.

**INTRODUCTION**

Viruses are responsible for a number of human pathogeneses including cancer. Several hard-to-cure diseases and complex syndromes including Alzheimer's disease, type 1 diabetes, and hepatocellular carcinoma have been associated with viral infections. Moreover, due to increased global travel and rapid urbanization, epidemic outbreaks caused by emerging and re-emerging viruses represent a critical threat to public health, particularly when preventive vaccines and antiviral therapies are unavailable. Examples include the recent emergence of dengue virus, influenza virus, measles virus, severe acute respiratory syndrome (SARS) virus, and West Nile virus outbreaks. To date, however, many viruses remain without effective immunization and only few antiviral drugs are licensed for clinical practice. The situation is further exacerbated by the potential development of drug-resistant mutants, especially when using viral enzyme-specific inhibitors, which significantly hampers drug efficacy. Hence, there is an urgent need to discover novel antivirals that are highly efficacious and cost-effective for the management and control of viral infections when vaccines and standard therapies are lacking. Due to the rapid emergence of deadly virus strains worldwide, the development of effective therapies for human viral diseases has become an emergency necessity. This is mostly dependent upon the identification of novel therapeutic agents with low toxicity. It is reported that plants have been used in medicines for thousands of years; in particular traditional medicines. Herbal medicines and purified natural products provide a rich resource for novel antiviral drug development. Identification of the antiviral mechanisms from these natural agents has shed light on where they interact with the viral life cycle, such as viral entry, replication, assembly, and release, as well as on the targeting of virus–host-specific interactions. These traditional medicines employing natural products have shown to contain antiviral compounds in vitro. The treasure troves of Ayurvedic & Siddha references and experiences passed over many decades channeled the development of a poly herbomineral formulation, which is a blend of antiviral phytomolecules and processed, purified, and detoxified form of natural metallic compounds. Under the stringent quality control process and GMP protocols, thus formulated products show significant antiviral property majorly by three mechanisms by

1. Inhibiting viral attachment, internalization, stimulating IFN-α secretion

2. Inhibiting the replication of the virus by producing an enhanced level of glutathione.

3. Inhibiting all proteases in the whole process of viral replication, and inactivating these proteases thus destructing the virus.

It is scientifically proven for its antipyretic, anti-inflammatory, and anti-bronchitis activities. The combined effect will reduce the viral infection and associated symptoms without any side effects. As the course duration is very small, just below a couple of weeks, the toxicity issues are out of curiosity. The formulation can play a vital role in therapeutics as a main antiviral agent or as catalysing and supporting therapeutic agents in antiviral therapy.

The study drug is a poly herbo-mineral formulation, which is a blend of antiviral phyto-molecules and processed purified and detoxified form of natural metallic compounds. It is a unique combination of *Lavanga (Eugenia caryophyllus), Ardraka (Zingiber officianale), Mustha (Cyperus rotundus), Parpataka (Hedyotis corymbosa), Ajamoda (Trachyspermum ammi), Hingula (Cinnabar, HgS), Haratala (Arsenic trisulphide)* and Pharmaceutical grade starch. Even though the study drug contains minerals such as HgS and As_2_S_3_ their dose is designed in such a way that there is no cumulative dose sufficient for making any type of toxicity in the continuous usage for maximum of 15 days. The drugs in the combination have showed marked antiviral, antipyretic and immune-modulatory effects. Hence it will be a great benefit to the humanity, if this drug is brought to the main stream of management.

**INVESTIGATIONAL PLAN**

**Overall Study Design**

This is a Randomized controlled, single blinded multi-center, comparative study of ZingiVir-H as an adjuvant therapy in hospitalized adults diagnosed with coronavirus disease 2019 (COVID-19). At inclusion, subjects who meet all inclusion criteria and no exclusion criteria will be assigned, in either therapeutic arm (ZingiVir-H), to receive ZingiVir-H in a dose of 500 mg tablet each consumed once in 3 hours ±1 hour between 6 AM and 9 PM in a given day (6AM, 9AM, 12Noon, 3PM, 6PM, 9PM) for a minimum duration of 10 days to Maximum 15 days OR will be on a Placebo arm to receive placebo (without active ingredients) each consumed once in 3 hours ±1 hour between 6 AM and 9 PM in a given day (6AM, 9AM, 12Noon, 3PM, 6PM, 9PM) for a minimum duration of 10 days to Maximum 15 days. The allocation of study arm is strictly as per the discretion of the Investigator. Whereas both the study groups shall be given standard of care of treatment as per the research site policies or COVID-19 therapeutic management policies. These doses will be administered orally. Blood samples for assessing CBC; safety laboratory tests and immunomodulatory markers will be obtained between baseline assessments (Day-01), during the day-06 of inclusion, at the end of the treatment day-15 and at the end of the study day-30. Safety-related assessments will include reports of adverse events and clinical laboratory test results.

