**Study Population**

Approximately 112 subjects will be randomized and considering 10% drop-out, the final evaluable subjects shall be 100.

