**Masking:**

Quadruple (Participant, Care Provider, Investigator, Outcomes Assessor)

**Duration of Treatment**: Minimum of Ten days to Maximum of Fifteen (15) days of study drug regimen and a follow-up on 30^th^ day from the day of baseline.

**Reference Therapy, Dosage and Mode of Administration**: Placebo and Standard of Care (SOC)

Placebo for this study is supplied as identically labeled, tablets. Placebo will also be required to be maintained in controlled environment as IP. Placebo must be consumed according to the same procedures and guidelines as ZingiVir-H.

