**Blinding**

Study drug will be assigned and administered in a Single blind fashion.

In the event of a medical emergency where it is imperative to know which treatment arm the subject was randomized to in order to make future treatment decisions, the Investigator may break the blind for an individual subject after getting approval from study monitor or sponsor. If any adverse events causing the need for subject unblinding, will be handled as a serious adverse event in accordance with the procedures outlined in this protocol. Any broken blind will need to be clearly justified, explained by a comment within the Case Report Form (CRF), and captured on the Serious Adverse Event Form.

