**Visit Schedule and Assessments**

**Screening / Randomization Visit – Day 01**

Subjects must meet the inclusion criteria and have none of the exclusion criteria in order to be eligible for randomization in this study. Subjects who meet all eligibility criteria, and have signed informed consent will be discussed randomize and move on to the Baseline study visit. Once the subject is randomized the sponsor representative or the study Investigator will provide the study staff with a unique randomization number for the subject.

Following assessments must be made at this Baseline visit for each study subject:

- RT-PCR test assuring the subjects test positive for COVID-19.
- Demographics
- Medical history (all known information regarding the subject’s health history/relevant surgeries/interventions prior to signing the informed consent).
- Vital signs: Body temperature, Pulse – beats per minute (BPM), Blood Pressure (BP) mmHg, Respirations – breaths per
- Concomitant medications (including medications, fluids and blood products administered within the 7 days prior to randomization).
- Documentation of any other infection if available (site of infection and, if available: positive culture results, prior antibiotics, sensitivity of cultured organism to antibiotics, nonmedical treatment such as surgery or drainage).
- Physical Examination including the following: general appearance, Head, Eye, Ear Nose Throat (HEENT), neck, respiratory, cardiovascular, chest, abdomen, lymphatic, musculoskeletal and extremities, skin and neurologic examination. Height and weight (baseline dry weight).
- Blood will be obtained for following laboratory tests:
  - Complete Blood Count with differential (Hemoglobin, Hematocrit, and WBC with differential count) & ESR
  - Serum Chemistry- Creatinine, Urea, CRP, ALT, AST, Alkaline Phosphatase, Albumin, total bilirubin
  - Pregnancy test; Serum or Urine human Chorionic Gonadotropin (hCG) - Pregnancy test only required for woman of childbearing potential on the day of randomization
  - Immunomodulatory markers, IL6, IL7, Interferon α, IgG, IgM

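### The protocol contradicts itself on how arms are assigned: it calls the trial randomized 1:1, yet its design section leaves allocation to the investigator's discretion

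*Protocol*

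**What the plan says.** The Overall Study Design section of the protocol opens with "This is a Randomized controlled, single blinded multi-center, comparative study of ZingiVir-H". After describing the active and placebo arms, the same paragraph states: "The allocation of study arm is strictly as per the discretion of the Investigator".

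Elsewhere the protocol presumes randomization:

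- Statistical Methods (synopsis): "This sample size is allocated to treatment arms in a 1 to 1 ratio".
- Study Population: "Approximately 112 subjects will be randomized and considering 10% drop-out, the final evaluable subjects shall be 100".
- Inclusion criterion 3 times the PCR test relative to randomization.
- Screening / Randomization Visit, Day 01: once a patient has been randomized, "the sponsor representative or the study Investigator will provide the study staff with a unique randomization number".
- Blinding: the emergency provision covers cases where "it is imperative to know which treatment arm the subject was randomized to".
- Data Management, Documentation: the subject number is built from the site number and the randomization number.

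On blinding, the Overall Study Design and Blinding sections say single blind ("Study drug will be assigned and administered in a Single blind fashion"). The Masking entries, in the synopsis and in the body, say "Quadruple (Participant, Care Provider, Investigator, Outcomes Assessor". The Blinding section also requires the investigator to obtain approval from the monitor or sponsor before breaking the blind for a patient.

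**The concern.** Random allocation and allocation at the investigator's discretion exclude each other. The discretion sentence stands in the operative design section, directly after the two arms are described, and is worded without exception. No other section says how a random sequence is generated, who holds it, or how it is concealed. The discretion sentence is therefore the only explicit statement of what determines a patient's arm.

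With up to five sites, some could follow that sentence and others the randomization visit. Where the sentence is followed, a view of the patient's prognosis can influence the arm, and the two groups need not be comparable. Statistical Methods names the t-test, rank-sum test and Fisher's exact test, all unadjusted. With discretionary allocation, neither the p-values nor the Day 15 odds ratio could be read as the effect of treatment.

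**Working it through.** **1. Setting the statements side by side**

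| Statement | Section | Compatible with the investigator choosing the arm? |
|---|---|---|
| Study is randomized | Overall Study Design | No |
| 1:1 allocation of the sample | Statistical Methods | Not as part of a randomized design |
| 112 subjects to be randomized | Study Population | No |
| PCR timed against randomization | Inclusion Criteria | No |
| Randomization number issued | Day 01 visit | Presumes randomization has already happened |
| Arm the subject was randomized to | Blinding | No |
| Subject number uses randomization number | Documentation | Presumes randomization |
| Investigator masked | Masking | No: whoever chooses the arm knows it |
| Approval needed before investigator unblinds | Blinding | No: implies the arm is unknown to the investigator |
| Single blind | Overall Study Design, Blinding | Yes, if only the patient is blinded |
| Allocation at investigator's discretion | Overall Study Design | This is the conflicting rule |

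One sentence stands against many, but none of the others limits or cancels it.

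**2. The plan's own figure**

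The contradiction rests on no number. The one related figure reproduces: 100 evaluable with 10% drop-out gives 100 / (1 − 0.10) = 111.1, rounded up to 112. Correcting the allocation rule leaves it unchanged.

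**3. Illustration of what discretionary allocation could do**

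From the protocol: 100 evaluable split 1:1, so 50 per arm; Fisher's exact test for categorical variables; significance at 0.05, with sidedness not stated and taken here as two-sided.

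Assumed, not in the protocol: the drug has no effect; half the patients have a good prognosis and half a poor one; 85% of the good and 55% of the poor improve by Day 15; the ordinal outcome is reduced to improved or not; a share q of the active arm and 1 − q of the control arm has a good prognosis.

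Expected improvement:

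- active: pA = 0.85q + 0.55(1 − q)
- control: pC = 0.85(1 − q) + 0.55q
- spurious odds ratio: [pA / (1 − pA)] / [pC / (1 − pC)]

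For q = 0.60: pA = 0.51 + 0.22 = 0.73 and pC = 0.34 + 0.33 = 0.67, so the odds ratio is (0.73/0.27) / (0.67/0.33) = 1.33.

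For q = 0.70: pA = 0.595 + 0.165 = 0.76 and pC = 0.255 + 0.385 = 0.64, so the odds ratio is (0.76/0.24) / (0.64/0.36) = 1.78.

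The false-benefit rate is the summed binomial probability of all 2×2 tables with two-sided Fisher p < 0.05 and more improvement on active:

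| Good-prognosis share, active / control | pA | pC | Odds ratio | False benefit |
|---|---|---|---|---|
| 50 / 50 (random allocation) | 0.70 | 0.70 | 1.00 | 1.5% |
| 60 / 40 | 0.73 | 0.67 | 1.33 | 6.5% |
| 70 / 30 | 0.76 | 0.64 | 1.78 | 19.6% |

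The reference value is 1.5% rather than 2.5% because Fisher's test is conservative at this size.

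Other assumed improvement rates give the same pattern. With 80%/50% the false-benefit rates are 1.5%, 6.2% and 18.2%; with 90%/60% they are 1.5%, 7.0% and 21.7%. The calculation is symmetric: if discretion sent the better-prognosis patients to placebo, the same rates would apply to a false disadvantage, and a real benefit could be hidden.

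**The case against.** The strongest defence is that the discretion sentence is a drafting slip. Almost everything else presumes randomization, and the masking and unblinding text makes little sense if the investigator knows the arm. This is fair evidence that a random list was intended. It does not settle the matter, because the sentence is current body text, is emphatic, and is nowhere withdrawn. The blinding text is itself divided, so it cannot decide the question.

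A second defence is that randomization mechanics are often kept in a separate plan. That would answer a complaint about missing detail. It does not answer an allocation rule that the protocol states and that is incompatible with randomization.

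Three stronger readings are tempting but not supported:

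- A reader might infer that the investigator does choose every patient's arm. The document leaves two conflicting rules open and does not say which one sites apply.
- A reader might infer that the same investigator also judges the primary endpoint. The Primary Efficacy Endpoint and Ordinal Scale assessment sections do not say who scores the scale, and the Masking entries list a masked outcomes assessor separately from the investigator.
- A reader might take the Day 01 visit text as a second grant of discretion. It has a number passed on after randomization, which is not choosing an arm. It is a secondary weakness in concealment only.

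It also stands that the inputs to the illustration are assumed. The rates are not an estimate for this trial.

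**Conclusion.** The protocol is wrong as written and must be corrected: its design section states an allocation rule that cannot coexist with the randomized design it claims. If that rule is followed, the trial is neither randomized nor concealed, and the unadjusted between-group comparisons lose their basis.

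The conclusion about the contradiction rests on the text alone and needs no assumption. The size and direction of any bias are unknown. On the assumed inputs, across the three pairs of improvement rates, a moderate imbalance (60/40) raises the false-benefit rate from 1.5% to about 6–7%, and a larger one (70/30) to about 18–22%. These figures show only that modest steering would matter in a trial of this size.

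**What to change.** - In Overall Study Design, delete the sentence giving the investigator discretion over the arm.
- State in its place that allocation is 1:1 from a pre-generated random list, held by someone outside enrolment and concealed from the enrolling investigator until consent and eligibility have been recorded.
- In the Day 01 visit section, remove the investigator as a possible source of the randomization number.
- Reconcile the single-blind statements with the quadruple-masking entries, so that it is clear whether the investigator is masked.
- If any patients have already been assigned by discretion, identify them and report them as non-randomized. An amendment cannot make them randomized.

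The cost is one protocol amendment and one randomization list. The planned 112 is unchanged. Block sizes, stratification and the means of concealment can be set out in a randomization plan.
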